#### Surveys

4.9.3

Surveys will be electronic, with hard copies provided upon request. The surveys will include physical activity (T1, T2, T3), demographic (T1, T2, T3), health (T1, T2, T3), travel (T1, T2, T3), and changing circumstances (T2, T3) questions. The surveys have been adapted for young people as appropriate—removing questions suitable for adults only (e.g. marital status, height/weight, certain health conditions/behaviours) or including questions relevant to young people only (e.g. physical activity within the school setting).•*Physical activity questions:* The International Physical Activity Questionnaire – Long form (IPAQ-L) is reliable and widely used and will capture transport-related, leisure time, occupational, domestic and total physical activity and sedentary time at T1, T2 and T3 [42]. For young people only, questions related to physical activity within the school setting from the IPAQ-A were included [43].•*Demographic questions:* At T1 only: gender, date of birth, and language spoken at home. At T1, T2 and T3: highest level of education, student status, employment status, household composition, residential and work/study address, and income. Additionally, adults at T1, T2 and T3 will be asked about marital status and work from home arrangements.•*Health-related questions:* Adult participants only: height and weight using standard measures; if they have ever (and if current) been told by a doctor that they have high blood pressure, heart disease, stroke, diabetes, cancer, osteoporosis, depression or anxiety, or arthritis (Tasmanian Population Health Survey items [44]); current smoking [44]; illness/injury/disability that limits physical activity or bus use. All participants will be asked to rate their health ranging from excellent to poor. Health-related data will be collected at T1, T2 and T3.•*Travel-related questions:* At T1, T2 and T3 motorised vehicle access and ownership, access to equipment for active travel e.g. bicycle, driver's license, transport mode and frequency, time and distance to nearest bus stop (from home and work/study) and enablers/barriers of bus use. A simple paper-based seven-day travel diary completed at T1, T2 and T3 will capture mode, duration, and frequency of public, private, and active travel. Use of TravelVu will be encouraged—a freely available travel app that captures travel information per trip which will aid diary completion through better recall [45]. If participants use TravelVu they will be encouraged to send these data as a.csv file by email to a designated staff member.•*Economic evaluation questions:* Adult participants only: time spent commuting, use of time whilst commuting, work productivity and transport-related costs (e.g. walking equipment, fuel, parking) at T1, T2, T3•*Changing circumstances questions:* At T2 and T3: changes in health, home, or work circumstances, travel characteristics, or contact details.•*Process evaluation:* At T1, T2 and T3, participants will be asked to evaluate study materials, correspondence, intervention impact, report on their motivations for participating and staying involved in the study and provide general feedback.

The survey will be pilot tested on a convenience sample of individuals ≥15 years (e.g. family members and colleagues of the research team, staff from partner organisations, Consumer Advisory Group members) as another strategy to ensure suitability, completion and retention. Pilot testing data will not be retained.

### Statistical methods

4.10

Quantitative analyses will be conducted using Stata (17.0, StataCorp LLC, College Station, TX). Descriptive statistics will characterise participants, acceptability, and outcomes according to group allocation. Primary intention-to-treat analyses will focus on comparing change in daily steps from baseline (T1) to 14 weeks (T2). A random-intercepts linear regression model with covariates for T1 steps, time (1 = T2, 0 = T1), baseline steps x time, and group (1 = intervention, 0 = control) x time will be estimated. The efficacy of intervention (primary outcome) at T2 will be assessed from the coefficient of group × time (equivalent to an analysis of covariance, and to a change scores method when a T1 steps covariate is included, though standard errors may differ slightly). The advantage of this model is that it can be readily extended to analysis of a third time-point to test whether intervention efficacy is maintained at 39 weeks (T3). Prior to analysis, right-skewed physical activity data will be transformed using a logarithmic transformation, which worked well with the *trips4health* trial data. All models will be estimated without and with adjustment for T1 participant characteristics that differ materially between groups.

Individual-level time spent commuting, use of time whilst commuting, work productivity and financial outlay for transport (e.g. walking equipment, fuel, parking) will be analysed as part of the economic evaluation. Non-research related costs and benefits of intervention implementation relative to the control group will be assessed. Modelled analyses will assess the financial implications of broader implementation rollout and upscaling of the intervention.

Process evaluation will assess the fidelity and quality of implementation, clarify causal mechanisms and identify contextual factors associated with outcome variation. The Medical Research Council (United Kingdom) framework will underpin the process evaluation as it is designed to examine complex public health interventions [46]. Process evaluation will involve face-to-face or telephone/video interviews (n = 10) with intervention participants (who did and did not reach bus targets). Administrative and research data may be used in process evaluation analysis. Qualitative process evaluation data will be analysed thematically using NVivo software (QSR International, Doncaster, Victoria, Australia).

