### Eligibility criteria

4.2

Potential participants will be screened by online survey or telephone. The self-assessed inclusion and exclusion criteria are listed in Box 1. Those eligible will receive an information sheet and provide online or verbal consent.Box 1Self-assessed inclusion and exclusion criteria**Table undtbl1:** 

Inclusion criteria
• ≥ 15 years
• Tasmanian resident
• sufficient English proficiency to provide informed consent
• possession of a mobile phone and active email address
• ownership of or willingness to obtain a Metro Greencard (travel smartcard)
• willingness to give permission for the researchers to access smartcard data
• currently making no more than five Metro bus trips/week
• able to reasonably access a Metro bus service
• currently making trips by motor vehicle (including motorcycle) that could be made by bus
Exclusion criteria
• intending to move house or work location within the study period whereby a Metro bus service will be inaccessible
• currently engaged in or planning to engage in other public transport incentives program
• pregnancy
• a health condition that prevents walking
• a health condition that prevents bus use
• a planned activity that would prevent bus use for greater than four weeks during the 14-week intervention phase of the 38-week study period (e.g. surgery, extended holiday)Alt-text: Box 1

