### Sample size

4.6

At least 345 participants will be randomly allocated across both study arms—an oversampling of 15 % to allow for attrition (based conservatively on *trips4health* and the relevant ACHIEVE study [12,18]) leaving a minimum of 300 participants. Three hundred participants will provide 80 % power (two-sided α = 0.05) to detect a 34 % change (∼2500 steps/day) in daily steps in the intervention group relative to controls (primary outcome) and meaningful increases (13–29 %) in secondary outcomes. The power calculation is based on the standard deviation of change in the physical activity outcomes, log-transformed due to the right-skewed nature of physical activity data (Table 3).

**Table 3 tbl3:** Increase in outcomes detected with n = 300.

Outcomes	Standard deviation of change (log scale)^a^	Relative increase in outcome
Accelerometer (steps/day)	0.336	11.5 %
Transport-related physical activity (hours/week)	0.790	29.1 %
Bus use in week (trips/day)	0.390	13.4 %

a Standard deviation estimates from *trips4health*.

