### Assignment of interventions

4.8

Once participants have completed T1 they will be randomly allocated to the control or intervention arm. Randomisation will be allocated on a 1:1 ratio in blocks of four, without stratification. The allocation sequence will be created using a pseudo-random algorithm in Stata (17.0, StataCorp LLC, College Station, TX) with a true random seed number between 1 and 1,000,000 [35]. The allocation sequence will be executed in Research Electronic Data Capture (REDCap, Version 13.7.31, Nashville, Tennessee, USA). Research team members who enrol participants in the respective study arms will not have access to the randomisation details.

Participants cannot be blinded to treatment allocation given the intervention type. All members of the research team will be blinded except for the research assistants. Unblinded staff will enrol participants, assign participants to the control or intervention arms as per the treatment allocation sequence generated, inform participants of the study requirements according to intervention/control group allocation and be the main contact point for participants. Unblinded staff will not analyse data. The research team member who creates the randomisation sequence will not contact participants, nor administer data collection. All other research team members (investigators, data analysts, postgraduate students) will be blinded. The need to unblind other research team members is unlikely.

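### The 13.4 % detectable increase in bus use sits on a log scale that does not fit a population including people who make no bus trips, and its unit and zero handling are not stated

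*Protocol article*

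**What the plan says.** **Scale of the analysis.** Section 4.10 (Statistical methods) states that "right-skewed physical activity data will be transformed using a logarithmic transformation", adding that this worked well on the data of the earlier trial, *trips4health*. It mentions no added constant and no rule for zeros.

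**Scale of the power figures.** Section 4.6 (Sample size) bases power on the SD of change after log transformation. Table 3 lists three outcomes with a log-scale SD and the relative increase detectable with 300 participants: steps (0.336; 11.5 %), transport-related physical activity in hours/week (0.790; 29.1 %), and bus use (0.390; 13.4 %). The bus row is labelled "Bus use in week (trips/day"). The SDs come from *trips4health*.

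**Definition of the outcome.** Table 2 (section 4.4) defines smartcard bus use in trips/week. Section 2 makes bus use and transport-related physical activity the two secondary hypotheses.

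**Who is enrolled.** Box 1 (section 4.2) requires people to be "currently making no more than five Metro bus trips/week", with no lower limit, and accepts "ownership of or willingness to obtain a Metro Greencard (travel smartcard").

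**The concern.** Someone who does not use the bus, or has no smartcard yet, has zero trips on record before entry. Controls receive no bus incentive, so zero-trip weeks should also be expected among them later. A logarithm cannot take a zero, which leaves two ways of staying on the log scale:

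- **Leave zeros out.** This removes non-users. Where the zero falls after randomisation, it also selects people on their outcome.
- **Add a constant before taking logs.** Everyone stays in, but the back-transformed effect is a ratio of (trips + constant). It equals no single percentage increase in trips, and it changes with the constant and with the unit. The unit is itself in doubt, since Table 3 and Table 2 disagree.

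Either way, a reader cannot tell from Table 3 how many extra trips the trial can detect. That matters because the intervention itself aims at small numbers: Table 1 sets weekly target increases of one to four trips.

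**Working it through.** **1. Reproduce Table 3.** Inputs from section 4.6: "two-sided α = 0.05", 80 % power, 300 analysable participants. Section 4.8 gives 1:1 allocation, so 150 per arm. For a two-sample comparison of mean log change (normal approximation):

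δ = SD × (1.960 + 0.842) × √(2/150) = SD × 2.8016 × 0.11547; detectable relative increase = exp(δ) − 1.

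| Outcome | SD (log) | δ | Recomputed | Table 3 |
|---|---|---|---|---|
| Steps | 0.336 | 0.1087 | 11.5 % | 11.5 % |
| Transport-related activity | 0.790 | 0.2556 | 29.1 % | 29.1 % |
| Bus use | 0.390 | 0.1262 | 13.4 % | 13.4 % |

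The arithmetic is right. The question is what the 13.4 % is a percentage of.

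**2. How often a zero week could occur.** The documents give no share of zeros. Assuming Poisson weekly counts, P(0) = exp(−mean): 61 % at a mean of 0.5 trips/week, 37 % at 1, 14 % at 2 and 5 % at 3. With an unchanged mean and two independent weeks, the chance of a zero in at least one is 1 − (1 − P(0))²: 85 %, 60 %, 25 % and 10 %.

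**3. What 13.4 % means with an added constant.** Assume, for illustration only, a constant of 1. Then new value = (x + 1) × 1.134 − 1.

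- From 2 trips/week, applied to trips/day: (2/7 + 1) × 1.134 − 1 = 0.458/day = 3.21/week, or +1.2 trips/week.
- From 2 trips/week, applied to trips/week: (2 + 1) × 1.134 − 1 = 2.40, or +0.4 trips/week.

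| Starting trips/week | Gain, constant on trips/day | Gain, constant on trips/week |
|---|---|---|
| 0 | +0.94 | +0.13 |
| 1 | +1.07 (107 %) | +0.27 (27 %) |
| 2 | +1.21 (60 %) | +0.40 (20 %) |
| 5 | +1.61 (32 %) | +0.80 (16 %) |

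At 2 trips/week the two units differ threefold. No cell with a defined percentage equals 13.4 %. A smaller constant brings the percentage closer: 0.1 on trips/week gives 14.8 % from 1 trip and 13.7 % from 5.

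**4. Does the SD of 0.390 show which route was taken?** Take two independent single-week Poisson counts with the same mean, between 1 and 5 trips/week, and no true change (assumption). Counting noise alone gives these SDs of log change:

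- zeros dropped: 0.63 to 0.80;
- log(trips/week + 1): 0.59 to 0.72;
- log(trips/day + 1): 0.17 to 0.26.

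The first two ranges exceed 0.390. The third leaves room for real change to bring it up to 0.390. A constant added to trips/day is therefore plausible, but not shown: averaging trips over several weeks would also lower the SD.

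**5. If zeros were dropped instead.** Holding the SDs fixed and losing 10, 30 or 50 % of participants (assumed), the same formula gives detectable increases of 14.2, 16.3 or 19.5 % for bus use and 30.9, 35.7 or 43.5 % for transport-related activity.

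**The case against.** **The log sentence concerns physical activity data, not bus trips.** Correct. The log scale reaches bus use only through Table 3, so the point about trips rests mainly on that table. The table does, however, state the effect on that scale.

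**Zero rules and secondary models belong in the analysis plan.** The details of a model may. But the detectable effect, its scale and its unit are fixed in this article, and a later document cannot turn a ratio of (trips + constant) into a relative increase in trips.

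**The transformation worked in the earlier trial, and the figures reproduce.** Both statements stand. Zeros may have been handled sensibly there. The article does not say how, and reproducing the arithmetic does not settle what the percentage refers to.

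**Averaging over weeks would thin out the zeros.** This also stands. Table 2 includes smartcard data across the whole T1–T2 period, and six months of earlier data are retrieved for existing cardholders. Averaging lowers both the share of zeros and the SD, but does nothing for someone with no trips at all or no card.

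**Stronger readings.** A reader might infer that both secondary analyses are unsound, that the trial will exclude people with zeros, or that eligibility makes zero transport-related activity common. The documents support none of these. The detectable effects follow from the stated SDs, no exclusion is proposed, and Box 1 limits bus trips only, not walking, cycling or other active travel.

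**Conclusion.** The point holds in a limited form. Table 3 expresses the bus-use effect as a relative increase on a log scale, in a unit different from that of the defined outcome, for a population in which zero-trip weeks must be expected. Unless the unit and the handling of zeros are stated, the 13.4 % cannot be translated into trips. At a starting level of 2 trips/week it could mean about +0.4 or about +1.2 trips/week. Those two values rest on an assumed constant of 1 and an assumed starting level, so they show sensitivity and are not corrected figures; no single corrected figure can be computed from the article. For transport-related hours the same concern applies under the log rule of section 4.10 only as far as zeros occur, and their share is unknown. The primary steps analysis is not affected.

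**What to change.** - **Smartcard bus trips:** analyse as counts with a negative binomial model, or a Poisson model with robust standard errors, with an offset for the weeks observed. Report a rate ratio and an absolute difference in trips/week.
- **Transport-related hours:** use a method that keeps zeros, for example ANCOVA on the raw scale with robust or bootstrap standard errors. Exclude nobody because a value is zero.
- **Table 3:** state the unit and any constant behind the 0.390 and 0.790, align bus use with the trips/week of Table 2, and restate both secondary detectable effects in trips and in hours.
- **Steps/day:** no change to the log analysis is needed on this account.

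The cost is wording and standard Stata commands, plus a look back at how the *trips4health* SDs were obtained. The downside is that the restated secondary detectable effects may look less favourable.

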### Data monitoring

4.11

#### Harms

4.11.1

Physical activity intervention studies pose minimal risk to participants [47]. The most common (but unlikely) physical activity intervention study-related adverse events are minor musculoskeletal injuries [47]. Adverse events will be logged in REDCap, reviewed by the nominated clinician chief investigator to determine the appropriate action and reported to the ethics committee. Participants disclosing existing health conditions/injuries that limits bus use will be encouraged to seek advice from their health practitioner before study participation. Participants in the intervention group will be provided with a ‘Checklist’ with tips for safe bus travel; as control group participants are not being encouraged to catch the bus more, they will not receive this checklist.

At study end, participants will be provided with summary health-related information (e.g. physical activity and for adults only body mass index). Participants will be encouraged to share this summary information with their health care practitioner, especially if values are outside normal limits or physical activity targets are unmet.

#### Auditing

4.11.2

Audits will be conducted after approximately 10 % and then 50 % of the total sample have completed week two of the intervention phase. At each audit, an unblinded staff member will check study operationalisation (e.g. consent forms signed and stored, randomisation process working, surveys complete, data stored appropriately, correct and timely correspondence to participants, bus trip incentives correctly allocated).

### Ethics and dissemination

4.12

#### Protocol amendments

4.12.1

Protocol amendments will be submitted to the Tasmanian Health and Medical Human Research Ethics Committee for approval. Where required, relevant parties will be notified of protocol changes. If any protocol changes directly impact participants (e.g. changed eligibility criteria), participants will be asked to re-consent.

#### Consent

4.12.2

Participants will provide consent electronically (online) or verbally (by a staff member via telephone) using our RedCap data captures system. Consent forms will be stored securely and separate to study data. Due to the intervention type (financial incentive), the extent of data collection, and study length, young people 15–17 years old will be directed to a consent form to be co-signed by a parent/carer. If a young person is living independently from their parent/carer and unable to gain their consent, they are legally able to give their own. In this case a member of the research team will discuss the study requirements with them.

#### Confidentiality

4.12.3

Research team members will have access to administrative data (e.g. names, contact details) only when necessary. For data cleaning and analysis, research data will be kept separately from administrative information. Only the unique identifier assigned to each participant will be used for data cleaning and analysis. Only investigators will have access to de-identified data. Study-related reports, publications and presentations will not include identifiable information. *Dissemination policy* An integrated knowledge translation plan will be informed by the Canadian Institutes of Health Research Guide to Knowledge Translation Planning [48]. The plan will include identifying the knowledge-user audience (beyond the research team), strategies (diffusion, dissemination, application), expertise (e.g. graphic design), and adequate resource allocation. Findings will be shared through traditional (e.g. journal publications and conference presentations) and non-traditional (e.g. social media) academic pathways. Authorship of academic output will abide by the National Health and Medical Research Council guidelines [49].

Participants will be provided with summary findings at study completion and offered summary personal information including body mass index (adults only) and a visual representation of their bus use and accelerometer derived physical activity. Participants will be alerted to any publicly available reports produced.

## Discussion

5

*Get BusActive!* will fill an evidence gap regarding the causal relationship between financially incentivised public transport use and physical activity. Although, *trips4health,* was abandoned due to the COVID-19 pandemic, the study was adequately progressed to provide informative preliminary and process evaluation data [18]. These data have been used to improve the study design of *Get BusActive! Get BusActive!* also includes several strategies to mitigate further potential pandemic impacts (e.g. no face-to-face study requirements).

The comprehensive measures collected through *Get BusActive!* (including objectively measured physical activity and bus use) will provide end-users (e.g. policy makers, public health officers) with valuable information to inform evidence-based decision making. End-users have been engaged since study inception (planning phase) and will continue to provide input across the study's life-cycle (ending with the sharing of findings). End-user engagement across the study's life-cycle increases study relevance, broadens reach and fosters more effective implementation of the findings. Engaging decision makers will also ideally lead to much needed “upstream” policy- or environmental-level interventions more likely to positively impact population-level physical activity [50].

However, this study is not without its limitations. The study setting is regional and therefore the findings may not be generalisable to urban environments or other regional settings where differences exist such as in the built environment, public transport provision and cultural and social norms. Further, despite heightened efforts to recruit harder to reach population groups, it is possible that over-representation of certain demographic characteristics will persist—the internal and external validity of the findings will be checked using census data of Tasmanian public transport users and the whole population.

